#### Resistance training

Resistance training consists of six exercises targeting the major lower and upper body muscle groups. The exercises can be delivered using the following modalities: machine-based, free-weights, or body-weight. All resistance exercises are individualized based on the patient’s fitness level, which is assessed by the trainer during the intake session using 12-repetition maximum (12-RM) muscle strength tests. Three sets per exercise are performed and the intensity is periodized (Table 1). To ensure a sufficient training load throughout the 9-month intervention period, the weights are continuously adjusted according to a progressive training protocol and in line with the periodization (if the participant’s health status permits) so that the predefined maximum number of repetitions is met as closely as possible. For participants with bone metastases, 12-RM testing is not performed for exercises that load regions with bone metastases (Table 2). Accordingly, adaptations to resistance exercises are shown in Table 2.

**Table 2 Tab2:** Adaptations to the prescribed exercise program based on location of bone metastases

Metastases site	Resistance exercise^**a**^			Aerobic exercise		Flexibility
	Upper	Trunk	Lower	WB	NWB	Static
**Pelvis**	**√**	**√**	**√**^c^		**√**	**√**
**Axial skeleton (lumbar)**	**√**		**√**		**√**	**√**^d^
**Axial Skeleton (thoracic/ribs)**	**√**^b^		**√**	**√**	**√**	**√**^d^
**Proximal humerus**		**√**^b^	**√**	**√**	**√**	**√**^b^
**Proximal femur**	**√**	**√**	**√**^c^		**√**	**√**
**All regions**	**√**^b^		**√**^c^		**√**	**√**^d^

This table is adapted from Galvão et al. (2011) [14]

^a^Resistance exercises that load the affected region can be either omitted according this table or can be performed using a “start low, go slow” approach, depending on patient characteristics and the experience of the involved trainer. According to this approach, participants with bone metastases should start with low weights and more repetitions and increase weights gradually over time up to 10-12 repetitions if possible. Higher intensities (i.e., 6–8 repetitions with 80–85% of h1RM) should be avoided. Weights will be reduced if participants report pain during a resistance exercise or experience an increase in pain or pain medication since the last exercise session

√ = Target exercise region

^b^exclusion of shoulder flexion/extension/abduction/adduction and inclusion of elbow flexion/extension

^c^exclusion of hip extension/flexion and inclusion of knee extension/flexion

^d^exclusion of spine/flexion/extension/rotation

*WB* weight bearing (e.g., walking), *NWB* non-weight bearing (e.g., cycling)

#### Unsupervised exercise program

In addition to the supervised exercise program, participants are encouraged to be physically active for at least 30 min per day on all remaining days of the week. The participants are provided with an activity tracker (i.e., Fitbit Inspire HR) and an exercise app specifically designed for the EFFECT study.

As indicated above, during the last 3 months of the program, one supervised session is replaced by one unsupervised session of 60 min, supported by the exercise app. The app includes exercises that participants have learned during the supervised exercise program and can be performed at home using body weight, free weights, or resistance bands. All exercises are illustrated with simple animations and contain clear instructions. Participants receive instructions on the use of the exercise app from the study team. Participants are supported by the trainer to effectively use the exercise app and to successfully make the transition to unsupervised exercise.

#### Control group

Patients randomized to the control group receive standard medical care. They do not receive a structured exercise intervention as this is not yet part of routine care. In line with current physical activity guidelines, the control group participants are advised to avoid inactivity and to be as physically active as their health status allows [9]. They also receive an activity tracker.

### Study outcomes

Patients visit the clinical center for measurements at baseline and 3 and 6 months post-baseline. This includes assessments of physical fitness, body composition, and blood markers (Table 3). For patients undergoing chemotherapy, these assessments take place at least three days after chemotherapy infusion. The primary outcome assessment is at 6 months. All questionnaires are completed at baseline, 3, 6, and 9 months post-baseline (Fig. 1). Socio-demographic data are assessed at baseline with a study-specific questionnaire. Medical data are retrieved from the medical records. Personal data are coded and all data are handled in compliance with the General Data Protection Regulation (GDPR) (EU) 2016/679.

**Table 3 Tab3:** Overview of all measurements in the EFFECT trial

		T0	T1	T2	T3
Outcomes	Instrument	Baseline	Month 3 ***± 14 days***	Month 6 ***± 14 days***	Month 9 ***± 21 days***
**Primary outcomes**					
**Cancer-related fatigue**	EORTC QLQ-FA12	X	X	X	X
**Health-related quality of life**	EORTC QLQ-C30	X	X	X	X
**Secondary outcomes**					
**Patient-reported outcomes**					
**Breast cancer-specific symptoms**	EORTC QLQ-BR45	X	X	X	X
**Depression and anxiety**	Patient Health Questionnaire (PHQ-4)	X	X	X	X
**Sleep problems**	Pittsburgh Sleep Quality Index (PSQI)	X	X	X	X
**Pain**	Brief Pain Inventory Short Form (BPI-SF), PainDETECT, Pain Catastrophizing Scale (PCS)	X	X	X	X
**Quality of working life**^**a**^	Quality of Working Life Questionnaire for Cancer Survivors (QWLQ-CS)	X	X	X	X
**Subjectively measured physical activity**	Modified version of the GODIN questionnaire	X	X	X	X
**Productivity loss**	Productivity Cost Questionnaire (iPCQ)		X	X	X
**Healthcare resources consumption**	Medical Consumption Questionnaire (iMCQ)		X	X	X
**Health-related quality of life**	EQ-5D-5L	X	X	X	X
**Urinary incontinence**	International Consultation on Incontinence Questionnaire -Urinary Incontinence Short Form (ICIQ-UI SF)^b^	X	X	X	X
**Satisfaction with exercise intervention**^**g**^	Self-developed questionnaire		X	X	X
**Physical measurements**					
**Physical performance**	5-times sit-to-stand, short Fullerton Advanced Balance (S-FAB) scale	X	X	X	
**Physical fitness**	Steep Ramp Test (SRT), endurance cycle test, handgrip- and leg strength test, Cardiopulmonary Exercise Testing (CPET)^c^, Isokinetic and isometric peak torque^d^	X	X	X	
**Objectively measured physical activity**	Physical activity tracker (Fitbit Inspire HR)	X	X	X	X
**Muscle thickness**^**e**^	Ultrasonography	X	X	X	
**Body composition**	Bio-impedance, DEXA^f^	X	X	X	
**Anthropometry**	• Body weight	X	X	X	
	• Waist and hip circumference	X	X	X	
	• Height	X			
**Resting heart rate and blood pressure**	-	X	X	X	
**Blood markers**	Plasma, serum, buffy coat and peripheral blood mononuclear cells	X	X	X	
**Socio-demographic and medical data**					
**Socio-demographic data**	Self-developed questionnaire	X			
**Medical history and concomitant diseases**	Medical records	X	X	X	X
**Cancer progress and treatment over the course of the study**	Medical records	X	X	X	X
**Cancer characteristics and treatment history**	Medical records	X	X	X	X
**Concomitant medication**	Medical records	X	X	X	X
**Adverse events**	Reports of patients, trainers, oncology nurses, physicians or medical records	X	X	X	X
**Overall and breast-cancer-specific survival and progression-free survival**	Medical records and/or cancer registry	Up to 5 years after the 9-month intervention period			

^a^Add-on measurement in the following clinical centers: UMCU, NKI, DKFZ, and ACU

^b^Add-on measurement in the following clinical center: ONK, UMCU, and NKI

^c^Add-on measurement in the following clinical center: KI and DSHS

^d,e^Add-on measurement in the following clinical center: KI

^f^Add-on measurement in the following clinical center: KI and ACU

^g^Only for the exercise group

### Primary outcomes

The primary outcomes of the EFFECT study are cancer-related physical fatigue and health-related QoL (HRQoL). Cancer-related physical fatigue is measured using the questionnaire of the European Organization for Research and Treatment of Cancer (EORTC) that is specifically developed and validated for assessing cancer-related fatigue (EORTC QLQ-FA12) [15]. The EORTC QLQ-FA12 is a 12-item questionnaire and assesses physical, cognitive, and emotional dimensions of cancer-related fatigue. Scores range from 0 to 100 with a higher score indicating higher levels of fatigue. HRQoL is measured using the EORTC QLQ-C30 summary score, which includes all original QLQ-C30 subscales excluding the global QoL score and financial difficulties score [16, 17]. Scores range from 0 to 100 with a higher score indicating a better HRQoL.

### Secondary outcomes

#### HRQoL, fatigue, anxiety, depression, sleep problems, and pain

Secondary outcome measures comprise the EORTC QLQ-C30/-BR45 functional and symptom scales and the other fatigue dimensions of the EORTC QLQ-FA12 (emotional, cognitive, and total fatigue scores). Anxiety and depression are assessed using the Patient Health Questionnaire for depression and anxiety (PHQ-4), which consists of two core anxiety items and two core depression items [18]. Sleep problems are assessed using the Pittsburgh Sleep Quality Index (PSQI), which contains 19 self-reported items assessing subjective sleep quality, sleep latency, sleep duration, habitual sleep efficiency, sleep disturbances, use of sleeping medication, and daytime dysfunction over the past month [19]. Pain is assessed using the Brief Pain Inventory Short Form (BPI-SF) and the Pain Catastrophizing Scale (PCS). The BPI-SF is a validated 11-item questionnaire and measures the severity of pain and its impact on daily functioning on a 0–10 numeric scale with the highest scores indicating worst pain and complete interference, respectively [20]. The PCS is a validated 13-item questionnaire designed to measure catastrophic thinking related to pain on a 0–4 scale with higher scores indicating a higher level of catastrophizing [21]. Neuropathic pain is assessed using the 13-item painDETECT screening questionnaire [22].

#### Resting heart rate and blood pressure

Resting heart rate and blood pressure are measured prior to the physical fitness and performance measurements (see Appendix II for details).

#### Physical fitness and performance

The order of the physical fitness and performance measurements is standardized. First, we assess functional performance and subsequently, MSEC, muscle strength, and aerobic capacity.

#### Functional performance

Originally, we planned to assess physical performance using the Short Physical Performance Battery [23]. However, due to the observation of ceiling effects in our first participants, we decided to replace this testing battery with the Short Fullerton Advanced Balance (S-FAB) scale [24] and the 5 times sit-to-stand test [23, 25]. The S-FAB scale measures static and dynamic balance during four tasks, including the tandem walk, standing on one leg, standing on foam with eyes closed, and stepping up onto and over a 6-inch bench. S-FAB tasks are rated on 0- (unable to complete task) to 4-point ordinal scale (independent task completion) with higher scores indicating better balance. The 5 times sit-to-stand test assesses functional strength of the lower limbs. The time (in seconds) required to perform 5 rises from the chair to an upright position as fast as possible is measured. This test is contraindicated for patients with spinal or pelvis metastases, who are unable to perform the test without impact on the spine/pelvis.

#### Maximal Short Exercise Capacity

MSEC is measured with the SRT using a cycle ergometer [26]. After 3 min of unloaded cycling, the test starts at 25 Watts and is increased by 2.5 Watts per second or 25 Watts per 10 s until exhaustion. Participants are instructed to cycle between 70 and 80 revolutions per minute (RPM). The test ends when cycling cadence drops below 60 RPM or when the participant experiences any pain or anxiety. After termination, the participant is asked to continue cycling at an easy cadence and with minimal load to recover. The outcome is registered as the highest achieved output in Watts and is referred to as MSEC. From the MSEC, peak Wattage (W_peak_) can be estimated using a regression equation [27]. Additionally, we record the RPE, time cycled, and heart rate at the end of the test as well as 1 and 2 min after termination.

#### Muscle strength

Upper body muscle strength is measured using a handgrip dynamometer (hydraulic Jamar®) with participants seated, their elbow by their side and flexed to the right angle (70°), and a neutral wrist position. Participants are asked to squeeze the dynamometer as hard as possible. Three measurements are performed on each hand and the best attempt of each hand is recorded. Lower body muscle strength is assessed using a leg-press hypothetical 1-repetition maximum (h1-RM) test according to a standardized protocol or an isokinetic dynamometer (IsoMed 2000®), unless the presence of bone metastases in the lower body prohibits safe testing. Measures of lower body muscle strength may differ between centers, but not within centers. For the h1-RM test, we record the highest weight that was successfully lifted for 12 repetitions and the corresponding h1-RM [28]. Maximal isokinetic peak torque (MIPT) is tested and recorded for each leg at 60°/s with the isokinetic dynamometer.

#### Aerobic capacity

Aerobic capacity is assessed using a constant-load exercise test to exhaustion on a cycle ergometer. The load is determined as 70% of the estimated W_peak_ derived from the SRT at baseline. If the SRT is terminated early and there are objective reasons to believe that a maximal MSEC was not achieved, 80% of the estimated W_peak_ is used as the load to avoid a ceiling effect of the test. Participants are instructed to maintain a speed of ~70 RPM. The test ends when cycling cadence drops below 60 RPM or when the participant experiences any pain or anxiety. After termination, the participant is asked to continue cycling at an easy cadence and minimal load to recover. The following parameters are recorded: time cycled in minutes, RPE, and heart rate at the end of the test as well as 1 and 2 min after termination.

#### Anthropometry

Anthropometric data (i.e., body weight, height, waist and hip circumference) are measured in light clothing without shoes (see Appendix II for details).

#### Body composition

Body composition (i.e., fat mass and fat-free mass) is measured prior to physical fitness testing by whole-body single frequency (50 kHz) bio-electrical impedance analysis (BIA). Patients are measured in a fasted state (no enteral intake for a minimum of 2 h) in a standing or lying position. Raw BIA data (i.e., reactance, resistance, and phase angle) are registered and estimates of fat mass and fat-free mass are obtained using the Kyle equation [29]. BIA devices may differ between centers, but patients within each center are measured consistently on the same device.

#### Blood markers

Plasma, serum, buffy coat and peripheral blood mononuclear cells (PBMC) are derived from whole blood samples (30 mL). In the 24 h prior to blood sampling, participants are instructed not to exercise vigorously or drink alcohol, and in the 2 h prior to blood sampling, they are asked to abstain from cigarettes, food, and drinks. Immediately after collection, blood samples are centrifuged and stored at -80°C at the local laboratory according to standardized procedures. Blood samples are transferred to the central biobank at the Karolinska Institutet for analysis after the last sample has been collected locally.

#### Physical activity

The Modified Version of the Godin-Shephard Leisure-Time Exercise Questionnaire and complementary questions on types and settings of exercise are used to measure self-reported physical activity levels [30, 31]. The Godin questionnaire is a 4-item questionnaire, including questions on the average frequency and duration one engages in mild, moderate, and vigorous aerobic activities and moderate-to-vigorous resistance exercises in bouts of at least 10 min during leisure time in a typical week. In addition, the Fitbit Inspire HR is used to objectively measure step count, heart rate, and physical activity minutes. Both intervention group and control group participants are asked to wear the activity tracker throughout the whole study period, but in any case during seven days after randomization and seven days before T1 (3 months), T2 (6 months), and T3 (9 months).

#### Cost-effectiveness

The EQ-5D-5L is used to measure health in five dimensions, including mobility, self-care, usual activities, pain/discomfort, and anxiety/depression, using 5 levels of severity [32]. This questionnaire is used to calculate quality adjusted life years (QALYs) during follow-up.

The actual costs incurred within both study arms will be compared until nine months after randomization. The cost-effectiveness analysis (CEA) will be done from a societal perspective, including healthcare costs, patient and family costs, and productivity costs. Participants are asked to complete questionnaires on these different types of costs. A health care use questionnaire was developed before the start of the study, based on the iMTA Medical Cost Questionnaire (iMCQ) [33], including cost categories that are deemed relevant for patients with mBC. Productivity losses are measured using the Productivity Cost Questionnaire (iPCQ) [34]. These questionnaires are completed 3, 6, and 9 months post-baseline.

#### Adherence

Adherence incorporates both attendance at the supervised exercise sessions and compliance with the prescribed exercises according to protocol. For each scheduled session, the trainer documents attendance and compliance in a case report form (see Appendix II for details).

#### Satisfaction

At 3, 6, and 9 months, we assess satisfaction with the supervised exercise program, the exercise trainer, the activity tracker, and supporting exercise app by means of a study-specific questionnaire.

#### Disease progression and survival

Participants will be followed for disease progression and survival for 5 years beyond the 9-month study period. Information on disease progression and (all-cause and breast cancer specific) death is retrieved from medical records and/or the cancer registry.

#### Add-on measurements

The following measurements are completed at some clinical centers (Table 3): quality of working life, urinary incontinence, cardiopulmonary exercise testing, whole body dual-energy X-ray absorptiometry, isokinetic and isometric peak torque, and muscle thickness. See Appendix II for details.

#### Safety

All (serious) adverse events ((S)AE) related to exercise or study measurements are recorded. Participants in both groups are asked by the study personnel about exercise- and study measurement-related (S) AEs in a standardized manner during all follow-up visits. In addition, participants allocated to the exercise group are asked by their trainer, before and after each supervised session, whether any potentially exercise-related (S) AEs occurred during or since the last exercise session. The trainers are instructed to contact the study team if any (S) AE occurred. All (S) AEs are recorded by the study team and SAEs are reported to the accredited ethical committee that approved the protocol, according to the requirements of that ethical committee.

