The skeleton is the most common site for distant metastases in breast cancer. In addition, patients can suffer from osteoporosis due to treatment with aromatase inhibitors [45]. Given the expected increased risk of skeletal-related events, including pathological fracture and spinal cord compression, exercise is often underutilized by trainers [46–48]. A recent systematic review showed that exercise is safe (no exercise-related SAEs were reported) and feasible for patients with bone metastases if it includes a supervised component [11]. In the current study, all exercise sessions are supervised by a trainer specially trained by the study team to ensure safe execution of the exercise program. Based on findings of the aforementioned review [11] and previous research in patients with advanced cancer [49], we provide all trainers with specific instructions on adaptations that need to be made to the prescribed exercise protocol in case of bone metastases. Nevertheless, exercise in patients with mBC remains challenging and additional adaptations to the exercise program may be required. Therefore, we have created an EFFECT exercise expert board that will respond to questions and request for additional information from the trainers. Additionally, members from all recruiting sites meet twice weekly to discuss exercise-related questions

In the curative setting, exercise programs from 12 weeks or longer are reported to be effective [9]. In the metastatic setting, patients generally receive continuous treatment. Therefore, we offer a longer intervention, i.e., a 6-month exercise program with 2 supervised session per week, followed by 3 months with one supervised exercise session replaced by one unsupervised session, which will be supported by an activity tracker and exercise app. Additionally, the trainer encourages the participant to be active in daily life. We hypothesize that the transition from supervised to unsupervised exercise sessions will help participants to maintain a physically active lifestyle beyond the period of study participation.

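### The scope of adverse event recording is stated inconsistently, and the exercise arm has an extra, far more intensive source of reports, so arm-wise counts that pool all sources would be biased.

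*Protocol article*

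**What the plan says.** The Safety section makes four statements about adverse events.

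- Scope of recording: "All (serious) adverse events ((S)AE) related to exercise or study measurements are recorded".
- Source common to both arms: "Participants in both groups are asked by the study personnel about exercise- and study measurement-related (S) AEs in a standardized manner during all follow-up visits".
- Additional source in one arm: "participants allocated to the exercise group are asked by their trainer, before and after each supervised session", the question being "whether any potentially exercise-related (S) AEs occurred during or since the last exercise session".
- Closing statement, without a relatedness limit: "All (S) AEs are recorded by the study team and SAEs are reported to the accredited ethical committee".

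Table 3 has an adverse event row marked at baseline and at 3, 6 and 9 months. Its sources are given as "Reports of patients, trainers, oncology nurses, physicians or medical records". The row has no relatedness limit and no footnote confining it to one arm.

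On visits, the Study outcomes section says: "Patients visit the clinical center for measurements at baseline and 3 and 6 months post-baseline". Questionnaires continue to 9 months.

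The Recruitment and randomization section says that participants, local study nurses and investigators cannot be blinded. The section on disease progression and survival takes progression and death from medical records or the cancer registry for all participants.

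**The concern.** Two features of the plan interact.

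The first is the relatedness filter. Someone has to decide whether an event is linked to exercise or to a trial measurement, and that person knows the allocation. Both arms undergo trial measurements, but only one has a structured exercise program. A fall or fracture in the exercise arm has an obvious candidate cause within the trial; the same event in a control does not. The visit question as worded also does not seek events put down to the disease.

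The second is unequal questioning. Frequent enquiry picks up minor and transient events that a three-month recall may lose.

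The two can push in opposite directions. An excess of events in the exercise arm could be detection, and a low count of related events could be attribution. This matters here because the Discussion itself raises the hazard: "Given the expected increased risk of skeletal-related events, including pathological fracture and spinal cord compression". Readers deciding whether to offer exercise to patients with bone metastases will look at the adverse event counts by arm, whether or not a formal test is attached.

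**Working it through.** The article states no safety figure, so there is none to reproduce. The check has two parts.

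**Scope statements side by side**

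| Place | Limited to related events? | Arms | Times |
|---|---|---|---|
| Safety, opening sentence | Yes (exercise or trial measurements) | Not specified | Not specified |
| Safety, visit question | Yes (same limit) | Both | All follow-up visits |
| Safety, trainer question | Potentially exercise-related, a looser test | Exercise only | Every supervised session |
| Safety, closing sentence | No limit stated | Not specified | Not specified |
| Table 3, adverse event row | No limit stated | No restriction | Baseline, 3, 6, 9 months |

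The closing sentence can mean the events just defined, or all events. Table 3 cannot settle this, because it names sources and times but not scope. Two sites could apply different rules and each point to the article.

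**Number of scheduled enquiries per participant**

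Inputs: two supervised sessions a week for 6 months, then one a week for 3 months (Exercise intervention section); two trainer enquiries per supervised session (Safety); follow-up clinic visits at 3 and 6 months (Study outcomes). The number of common contacts v is an assumption: 2 if only clinic visits count, 3 if the 9-month time point in Table 3 counts too.

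Sessions S = 2 × weeks in the first phase + 1 × weeks in the second phase:

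- 24 + 12 weeks: 48 + 12 = 60
- Table 1's 36 weeks, taking the change of phase after week 25: 50 + 11 = 61
- 26 + 13 weeks: 52 + 13 = 65

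Enquiries in the exercise arm = 2S + v; in the control arm = v.

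| S | v = 2 | Ratio | v = 3 | Ratio |
|---|---|---|---|---|
| 60 | 122 vs 2 | 61 | 123 vs 3 | 41 |
| 61 | 124 vs 2 | 62 | 125 vs 3 | 42 |
| 65 | 132 vs 2 | 66 | 133 vs 3 | 44 |

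Sensitivity:

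- At an assumed 80% attendance the ratio is 33 to 53. For example, S = 60, v = 3: (2 × 48 + 3)/3 = 33; S = 65, v = 2: (2 × 52 + 2)/2 = 53.
- At an assumed 50% attendance it is 21 to 34.
- Counting each session as one occasion, at full attendance, (S + v)/v is also 21 to 34. For example, (60 + 3)/3 = 21 and (65 + 2)/2 = 33.5.

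The imbalance is at least about twentyfold under every one of these assumptions. In months 7 to 9 the trainers still ask at one supervised session a week, while the article describes no clinic visit for either arm.

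**The case against.** The strongest reply is that the article promises safety monitoring and announces no between-arm safety test. Asking at each session is sensible supervision of an intervention and cannot be mirrored in an arm without sessions. The article is also a condensation: event definitions and reporting tables may be in the full protocol, which is not shown. All of this is fair and limits the weight of the point. It does not remove it, because the relatedness limit and the one-arm enquiry are stated rules, not omissions.

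Several stronger readings are tempting and are not supported.

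- *Only exercise-related events are recorded.* The opening sentence also covers trial measurements, which both arms undergo. Trainers ask about potentially related events, and no formal judging step is described.
- *Fractures or cord compression attributed to disease are certainly lost.* Table 3 lists physicians and medical records as sources without a relatedness limit, so the scope is unclear rather than plainly closed.
- *No fair between-arm comparison is possible.* The visit question is the same in both arms and is asked at the same visits. Progression and death are also collected alike. A comparison limited to visit-elicited related events has equal frequency of enquiry, though attribution stays unblinded.
- *The 9-month mark in Table 3 contradicts the visit schedule.* Patient reports and records do not need a visit.
- *The ratio of enquiries measures the bias.* It does not. Assuming, say, 90% detection with session enquiries and 50 to 70% without would give an apparent rate ratio of 0.9/0.7 = 1.3 to 0.9/0.5 = 1.8 under equal true rates. Nothing in the article supports those detection rates, and they are least plausible for fractures and cord compression, which medical records could reveal in either arm.

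**Conclusion.** The point holds in a limited form. The scope of recording is worded inconsistently within the Safety section and between it and Table 3. The exercise arm has an additional source of reports that runs to about 60 to 65 sessions at full attendance, against 2 or 3 common contacts. With unblinded attribution and a program in one arm only, arm-wise counts that pool the sources would be biased by detection and by attribution. The net direction is not certain. Over-recording of minor events in the exercise arm is the most plausible result, while attribution could work either way.

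The size of the bias cannot be estimated from the document. The session count rests on the stated schedule and on how 9 months is converted to weeks; the number of common contacts is an assumption. The primary outcomes are not affected. The point concerns how safety data are collected and tabulated, and an unseen full protocol may already resolve part of it.

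**What to change.** 1. Reconcile the Safety section with Table 3, so that one sentence says which events are recorded, in which arms and at which times, including 9 months.
2. In both arms, record all SAEs, together with fractures, other skeletal-related events and falls, regardless of judged relatedness. Keep relatedness as a recorded attribute, not as an entry condition.
3. Collect these through routes common to both arms: the standardized visit question at 3 and 6 months, widened to match, and the medical records and questionnaires already collected through 9 months.
4. Base any between-arm safety table only on these common sources.
5. Report trainer-elicited events in a separate descriptive table for the exercise arm, and say that the control arm has no counterpart.

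The cost is some protocol and analysis plan wording, a few case report form fields and more entries, most of them probably unrelated to exercise. Recruitment began in January 2020, so participants already enrolled would need retrospective capture from records. Falls that never reached medical care would be missed for them in both arms, and the report should say so.
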